### Randomisation

A computer generated random sequence will be performed using minimisation allocation with a 1:2 ratio to the back care advice and education group or back care advice and education plus pedometer-driven walking group [48]. To ensure adequate access to pedometers, randomised sequences will be created in blocks of 30 at a time (20 treatment: 10 control) and each allocation placed in a sealed blank envelop. As the self-management nature precludes double blinding, only the assessor for outcome measurements will be blinded to group allocation.

### Intervention

#### Back care advice and education

All participants will be given education and advice regarding self-management and the benefits of staying active [49]. Advice and education will take place in a single session, on a one to one basis for approximately one hour, by the research physiotherapist. Education and advice will be based on ‘The Back Book’ [50,51] which encourages a graded return to normal activities, addresses the nature of LBP, corrects unhelpful beliefs, and emphasises the need to use prophylactic pain control medication to allow activity [52,53]. The research physiotherapist will personalise the information using prior knowledge of the participant gained from clinical examination, baseline outcome measures and the pedometer trial results. Immediately following the back care advice and education session participants will be randomised into either the back care advice and education group or the back care advice and education plus pedometer-driven walking group.

#### Pedometer-driven walking programme

Participants allocated to the back care advice and education plus pedometer-driven walking group will undertake a physiotherapist-facilitated walking programme [21,54]. Each participant will be asked to wear a Yamax DigiWalker CW-701™ pedometer daily during the 12-week intervention period and record their daily steps in a walking diary. The aim of the intervention is to increase participants average daily step count. The walking programme is a behaviour change intervention in which the pedometer is used as a tool to help participants monitor their activity levels. The physiotherapist facilitates the process through the use of cognitive and behavioural techniques such as person-centred discussion of current activity behaviours, self-efficacy and barriers to increasing activity [55].

At week one, participants will undergo a 10 minute “self-efficacy walk” whilst wearing the pedometer [21]. The supervised self-efficacy walk assists participants in setting a walking goal (daily step count) they are confident in achieving over the following week. Participants return to see the physiotherapist at the end of week one to discuss any issues with the programme, pedometer or recording of desired information. A step target for week two will be agreed between the physiotherapist and the participant by referring to the mean daily step count recorded at baseline, the self-efficacy walk, and the average step count calculated from the walking diary. For weeks three to 12, the physiotherapist will phone each participant at a prearranged time, each week, to discuss his/her progress, document mean daily step count (recorded in diaries, and in the pedometer’s seven day memory) for the previous week, and agree to a new daily step target for the subsequent week. Throughout the walking intervention the physiotherapist will encourage participants towards self-management in goal setting, identifying suitable times and places for walking, dealing with any problems or difficulties that arise and refer to advice contained in the Back Book as appropriate. In this way the walking programme will be tailored to the individual.

Mean steps per day, for each week of the study will be calculated from participants’ daily records and will be used as both raw data and as change scores (numerical and percentage) recorded over the 12-week intervention period. Adherence to the walking group will be measured from participant reports of pedometer-derived data and calculated as a percentage of the prescribed number of steps completed [21]. Self-confidence and the belief that one can increase their PA through walking will be guided through the use of a five point self-efficacy scale developed by Marcus et al. [56]. High self-efficacy is related to reduced disability and the successful management of chronic conditions [57].

##### Focus groups

On completion of the 12-week walking programme, participants will be invited to participate in a focus group discussion designed to explore their thoughts and experiences of using pedometer-driven walking as a management tool for CLBP. Focus groups, led by an experienced moderator, will be established following every 30 participants who complete the walking programme. We anticipate recruiting five to six focus groups of six to eight people over the period of the study. One focus group will specifically recruit rural farm participants; conducted to address the feasibility of walking programmes in this setting. A checklist will be used to facilitate discussion on specific topics of interest to the researchers, yet at the same time allow for exploration of new topics or areas of interest to arise.

### Sample size

Given the non-invasive nature of a walking intervention likely carrying minimal health risk, we have chosen to use a 1:2 allocation ratio towards the walking intervention in order to increase confidence in interpreting or accepting any observed effect [58,59]. Results from the feasibility study informed initial calculations of sample size based on between group differences of 6–7 points in the ODQ. Given the wide confidence intervals expressed in these between group feasibility data and consdiering the recommended minimum important change of 10–12 points for individual improvement [60], we chose to first explore for an eight point between group difference. An 80% power calculation (alpha = 0.05), resulted in a minimum requirement of 174 participants (116 walking group, 58 standardised group). We anticipate a 15% loss to follow-up and will thus, aim to recruit 200 participants.

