**Methods/design:**

A fully-powered single-blinded randomised controlled trial will compare back care advice and education with back care advice and education followed by a 12-week pedometer-driven walking programme in adults with CLBP. Adults with self-reported CLBP will be recruited from the community and screened for elibility. Two-hundred participants will be randomly allocated to one of two intervention groups. All participants will receive a single back care advice and education session with a physiotherapist. Participants in the walking group will also receive a physiotherapist-facilitated pedometer based walking programme. The physiotherapist will facilitate the participant to monitor and progress the walking programme, by phone, on a weekly basis over 10 weeks following two face-to-face sessions. Outcome measures of self-reported disability, physical activity, participants’ low back pain beliefs/perceptions, quality of life and direct/indirect cost estimates will be gathered at baseline, three months, six months, and 12 months by a different physiotherapist blinded to group allocation. Following intervention, focus groups will be used to explore participants’ thoughts and experiences of pedometer-driven walking as a management tool for CLBP.

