#### Primary outcome

##### Self-reported functional disability

The Modified Oswestry Low Back Pain Disability Questionnaire (ODQ), a valid and reliable measure of pain and physical function in LBP patients, will be used as the primary outcome measure [35]. Ten questions, each with six options, assess an individuals’ perceived activity restrictions in daily tasks. A minimum score of zero and a maximum score of five is allocated to each question and summed. The recent UK *feasibility* study (n = 57) of pedometer-driven walking in people with CLBP demonstrated a 6 to 7 point between group difference at six months and will be used as a comparator in this study [21].

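### Recruiting 200 with 15% loss leaves 170, four below the stated minimum of 174; the 1:2 rationale is wrong for the between-group comparison, and power at the cited 6–7 points is only about 55–68%

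*Protocol article*

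**What the plan says.** All but two of the statements are in one paragraph of the protocol article, Methods/design, Sample size.

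- **Allocation.** Control to walking is 1:2, chosen "in order to increase confidence in interpreting or accepting any observed effect".
- **Target difference.** Initial calculations used "between group differences of 6–7 points in the ODQ" from the feasibility study. Citing that study's wide confidence intervals and the "recommended minimum important change of 10–12 points for individual improvement", the authors say "we chose to first explore for an eight point between group difference".
- **Size.** For 80% power at alpha 0.05 the minimum is 174: 116 walking and 58 control. Neither the standard deviation nor the sidedness of the test is given.
- **Attrition.** "We anticipate a 15% loss to follow-up and will thus, aim to recruit 200 participants".

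The section on the primary outcome says that the feasibility study (n = 57) "demonstrated a 6 to 7 point between group difference at six months and will be used as a comparator in this study". The abstract describes the design, without qualification, as "A fully-powered single-blinded randomised controlled trial".

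**The concern.** Three statements in the paragraph do not follow from its own figures or reasons.

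1. A target of 200 with 15% loss falls short of the minimum given in the sentence before it.
2. Unequal allocation is credited with strengthening confidence in the effect. For a comparison of two groups at a fixed total it does the reverse.
3. The target was moved above the only between-group difference cited. Wide pilot intervals express uncertainty in both directions, so they do not point to a larger value. A threshold for change in an individual is not a difference between group means, and 8 is not that threshold in any case. The move also reduces the number required.

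The third matters most for interpretation. If the true effect is the size seen in the study named as comparator, the trial has a substantial chance of missing it, and a null result could be read as coming from a fully powered trial.

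**Working it through.** **Inputs.** From Sample size: 58 control and 116 walking (174), target 8 points, power 80%, alpha 0.05, loss 15%, 200 recruited, feasibility difference 6–7 points. Assumed: a two-sided test, an unadjusted comparison of two means, and no information from participants who are lost.

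**Step 1: the recruitment target**
- Plan's figure reproduced: 174 × 1.15 = 200.1, that is, 200.
- Correct inflation: 174 / (1 − 0.15) = 204.7, that is, 205.
- Remaining from 200: 200 × 0.85 = 170, which is 174 − 170 = 4 short.
- Loss that 200 can absorb: 1 − 174/200 = 13%.

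**Step 2: implied standard deviation**

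The 174 cannot be verified because no SD is given, but it implies one. With z-values 1.960 + 0.842 = 2.802:

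SD = 8 / (2.802 × √(1/58 + 1/116)) = 8 / (2.802 × 0.1608) ≈ 17.76.

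A t-based calculation gives 17.66. A one-sided test would imply 20.01.

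**Step 3: power with 170 analysed**

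The SD cancels, because 80% at 8 points with 174 fixes the scale:

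power ≈ Φ(2.802 × (d/8) × √(170/174) − 1.960), where √(170/174) = 0.9884, so 2.802 × 0.9884 = 2.769.

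| True difference d | Argument of Φ | Power, 170 analysed | Power, 174 analysed |
|---|---|---|---|
| 8 | 2.769 − 1.960 = 0.809 | 79.1% | 80.0% |
| 7 | 2.423 − 1.960 = 0.463 | 67.8% | 68.8% |
| 6 | 2.077 − 1.960 = 0.117 | 54.7% | 55.6% |

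A noncentral t calculation with 57 and 113 analysed gives 79.2%, 68.0% and 54.8%. If the 174 was one-sided, the figures are 79.2%, 69.4% and 57.9%.

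For scale, at the same SD and 1:2 ratio, 80% power needs 228 analysed at 7 points and 312 at 6 points.

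**Step 4: cost of 1:2**
- Efficiency relative to 1:1 at the same total: 4 × (1/3) × (2/3) = 8/9 = 88.9%.
- Ratio of standard errors: √(9/8) = 1.061, so 6% larger.
- Analysed participants needed for 80% power at 8 points: 78 per arm, 156 in total, at 1:1, against 174 at 1:2.
- The 174 is already split 58 and 116, so this cost is inside the stated 80% and is not deducted again.

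**The case against.** **The shortfall is trivial.** The 80% is claimed only for 8 points, and there the loss is under one percentage point. This stands. A reader might infer that recruiting 200 fails to deliver the stated power in any meaningful sense; 79% against 80% does not support that.

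**The protocol never promises 80% at 6–7 points.** It calls that result a comparator, not the expected effect, and a trial may target a difference because it is worth detecting. This also stands: the choice of 8 is weakly argued, not miscalculated. But the reasons given do not support 8, and the abstract's claim of full power carries no such limit.

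**Confidence need not mean interval width.** The sources cited for the 1:2 sentence are not available here, and the article has purposes that a larger walking arm serves: uptake and adherence and feasibility in farmers (Aim and objectives), focus groups of walking participants (Focus groups), and within-group models (Statistical analysis). These can justify 1:2. They are not the reason stated, however, and the study hypothesis and the power calculation are both between-group. A reader might conclude that the ratio should change to 1:1. Given those aims it is a legitimate trade-off, and the documents do not support that step.

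**The planned analysis may do better.** Regression or mixed models could use partial data from participants who are lost, and adjustment could add power if it is not already in the 174. This is fair as a caveat, but the paragraph claims no such allowance.

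**Conclusion.** The point holds, as a matter of correcting stated figures and reasons.

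- **Attrition:** a genuine slip with a minor effect.
- **Allocation:** the stated rationale is wrong for the between-group comparison. It is not a second deduction from the 80%.
- **Target:** the chance of missing a true effect is about 45% at 6 points (100 − 55) and 32% at 7 (100 − 68). It would be too strong to say that a null result is nearly as likely as a positive one across the feasibility range. That fits 6 points; at 7 a positive result is about twice as likely.

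The power figures rest on the assumptions listed with the inputs and on the 174 having been calculated correctly. They do not depend on the undisclosed SD. The shortfall of four and the 8/9 efficiency need none of the power assumptions; the latter takes equal variances in the two arms.

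**What to change.** Make three wording changes, with no additional enrolment and no change to the allocation ratio.

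1. In Sample size, replace the attrition sentence with: *200 randomised, 170 analysed after 15% loss, about 79% power for 8 points and about 55–68% for 6–7 points*. Give the assumptions behind these figures. Alternatively, for the attrition arithmetic alone, state that 200 tolerates 13% loss; the power at 6–7 points should still be disclosed.
2. In the abstract, qualify the claim of full power as applying to an 8-point difference.
3. Replace the rationale for 1:2 with the purposes it serves (adherence, feasibility and focus-group data from the walking arm) and acknowledge the precision cost: a standard error 6% larger, or 174 analysed against 156 at 1:1.

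The cost is a few revised sentences and slightly less favourable published figures.

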### Statistical analysis

Multiple regression and/or mixed model analyses will be used to determine predictive models that best test for differences and changes in both outcomes and costs. Both within- and between group models will be used in order to determine whether use of a pedometer in the manner described in this study is a predictor of these outcomes. The change in ODQ from baseline will be the main dependent variable. Other outcome measures will be entered as alternate dependent variables to determine whether they significantly alter or provide a stronger model. Personal, occupational, seasonal, clinical and anthropometric variables will be entered into the model in a stepwise manner to seek the models that best explain changes in outcomes. Descriptive and statistical results for personal, demographic, anthropometric and outcome measures will be presented in tabular and graphic format.

Focus group discussions will be audio-recorded, transcribed and imported into NVivo 10 (QSR International) software for analysis. Thematic analysis using inductive methods will be used to identify core ideas important to participants’ experience, meaning and reality of pedometer-driven walking [61].

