##### Quality of life

Back pain significantly impacts quality of life [45]. Our study will use Quality Adjusted Life Years (QALYs) to estimate the impact of a walking programme on an individual’s quality of life. The EuroQol health survey instrument (EQ-5D-5 L) [46] is a self-administered survey tool that captures general health status. Participants rate their health on the day of testing over five domains (mobility, self-care, usual activities, pain/discomfort, and anxiety/depression) on a five-point scale and then score on a scale of 0 to 100 how their health today compares to their best (100) or worst (zero) health ‘imaginable’. An individual’s rating of each of the five health-related domains is summarised as a single score in the form of a utility estimate. The utility estimate will then be converted into a QALY for each participant and an average QALY for each group. We will compare the difference in QALYs at three, six, and 12 months.

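### Adjustment of the primary ODQ comparison for baseline ODQ is not secured, because change is the outcome and covariates enter only stepwise; fixing baseline in the model is a free gain in precision

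*Protocol article*

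**What the plan says.** Under Self-reported functional disability, the protocol article states that the Modified Oswestry questionnaire (ODQ) "will be used as the primary outcome measure". Under Statistical analysis it fixes the form of the outcome: "The change in ODQ from baseline will be the main dependent variable". The model is left open: "Multiple regression and/or mixed model analyses will be used to determine predictive models". The route by which covariates enter is stated: "Personal, occupational, seasonal, clinical and anthropometric variables will be entered into the model in a stepwise manner", with the aim of finding the best-explaining models. Baseline ODQ is not named among the covariates, and none is exempt from selection.

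ODQ is measured at baseline and at 3, 6 and 12 months (Study design; Outcome measures). Randomisation follows the advice session, which itself draws on the baseline measures (Back care advice and education). The baseline value is therefore available before allocation. Randomisation mentions minimisation in a 1:2 ratio but names no factors.

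Under Sample size the target is stated as "we chose to first explore for an eight point between group difference", with 80% power, alpha 0.05, a minimum of 174 (116 walking, 58 control), 15% expected loss and 200 to be recruited. No SD or correlation is given.

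**The concern.** Subtracting the baseline is not the same as adjusting for it. Unless r equals 1, change is negatively correlated with baseline, so an arm that happens to start worse tends to show more improvement even without a treatment effect. An unadjusted comparison of change keeps that noise, whereas a model containing baseline ODQ removes it.

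As written, whether the primary estimate is adjusted depends on whether baseline ODQ is offered to a data-driven selection step and survives it. What is at stake is precision, and how far the estimate in the one trial that is run can be moved by a chance baseline difference. Systematic bias is not at issue.

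**Working it through.** **Inputs.** From Sample size: difference 8, power 80%, alpha 0.05 (sidedness not stated; two-sided assumed), 58 and 116 analysed, 15% loss, 200 recruited. Not given and therefore assumed: the SD; r, taken over 0.3 to 0.8; and equal SDs at baseline and follow-up.

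**1. The plan's own figure.** With no SD stated, 174 can only be solved backwards.
- SD = 8 / [(1.960 + 0.842) × √(1/58 + 1/116)] = 8 / (2.802 × 0.1608) ≈ 17.8.
- An SD of 17.7 returns 58 + 116 = 174 with 80.2% power (normal approximation).
- This shows that 174 is consistent with an SD near 17.7. It does not reproduce the figure, and it does not say whether that SD belongs to change or to a single score.

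**2. Variance with and without baseline.** Let s be the SD of a single score.
- Change score: 2s²(1−r).
- ANCOVA: s²(1−r²).
- Ratio, ANCOVA to change: (1+r)/2. This is 0.65, 0.75, 0.80, 0.85 and 0.90 for r = 0.3, 0.5, 0.6, 0.7 and 0.8.
- For r = 0.5, 0.6 and 0.7, variance falls by 25%, 20% and 15%.

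**3. Power if the implied SD is the SD of change.** 200 × 0.85 = 170 analysed, taken as 57 and 113. I used the noncentral t with SD 17.66 × √ratio.

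| True difference | Unadjusted | r = 0.5 | r = 0.6 | r = 0.7 |
|---|---|---|---|---|
| 8 points | 79% | 89% | 87% | 85% |
| 6.5 points | 62% | 74% | 71% | 69% |

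The second row lies inside the 6 to 7 point difference that the article reports from the feasibility study.

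**4. Power if 17.7 is the SD of a single score** (8 points, 58 and 116 analysed, normal approximation).

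| r | SD of change | SD after ANCOVA | Power, change | Power, ANCOVA | Gain (percentage points) |
|---|---|---|---|---|---|
| 0.3 | 20.94 | 16.88 | 66.1% | 83.8% | 17.7 |
| 0.5 | 17.70 | 15.33 | 80.2% | 90.1% | 9.9 |
| 0.7 | 13.71 | 12.64 | 95.2% | 97.6% | 2.4 |

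**5. Chance imbalance.** Take 17.7 as the baseline SD.
- The between-arm baseline difference has a standard error of 17.7 × 0.1608 = 2.85 points, so a 95% range of ±5.6.
- If the arms differ by D at baseline, follow-up is expected to differ by rD with no treatment effect, and change by rD − D = −(1−r)D.
- At D = 5.6, the amount carried is about 3.9, 2.8 and 1.7 points for r = 0.3, 0.5 and 0.7, against a target of 8.

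**6. Would stepwise selection pick baseline up?** The correlation of change with baseline is −√((1−r)/2), or −0.59, −0.50 and −0.39 for r = 0.3, 0.5 and 0.7. With 174 analysed and an assumed entry level of p < 0.05, the chance of selection exceeds 0.99 for r up to 0.7 and is about 0.84 at r = 0.9. This applies only if baseline ODQ is a candidate, which the article does not state.

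**The case against.** The strongest reply is that nothing quoted is an error. Regressing change on arm and baseline gives the same treatment estimate as ANCOVA on the follow-up score, so change is harmless as an outcome once baseline is in the model. Baseline ODQ can be read as one of the clinical variables, and if offered it would almost surely be kept. A mixed model is also permitted, and depending on how it treats baseline it can recover most or all of the gain. A condensed article may leave the covariate list to a fuller plan.

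Most of this stands, and it limits the point. It does not remove it: the article states the route by which covariates enter, and that route leaves adjustment of the primary comparison to selection. Baseline ODQ is not named as a candidate, and the mixed model is only one option.

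A reader might be tempted by three stronger readings, which the document does not support:
- *That the change-score analysis is biased, or that imbalance passes straight through.* It is unbiased over randomisations, and only (1−r) of an observed baseline difference carries over. Because the minimisation factors are not named, balance on ODQ is neither assured nor excluded.
- *That the sample size is wrong.* If 17.7 is the SD of change, 80% with 174 analysed is consistent with an unadjusted analysis, and the loss is forgone precision.
- *That the QALY comparison has the same fault.* The article says "We will compare the difference in QALYs at three, six, and 12 months" but gives no QALY formula and does not say the comparison is unadjusted. A QALY total is also not a change score, so the mechanism would differ.

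**Conclusion.** The point holds as a no-cost improvement: the Statistical analysis section does not secure adjustment of the primary comparison for baseline ODQ. If baseline were left out, variance would be higher than it need be for every r below 1. The variance ratio follows from algebra under equal SDs, but its size here rests on an assumed r. The power figures also rest on a back-calculated SD whose meaning the article does not give. The gain is therefore a range: roughly 6 to 10 percentage points at 8 points with 170 analysed if the SD is that of change and r is 0.5 to 0.7, and about 2 to 18 with 174 analysed if it is that of a single score and r is 0.3 to 0.7. If baseline ODQ is offered to the stepwise procedure and retained, most of this loss does not arise. No stated figure is shown to be in error.

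**What to change.** State that the primary between-group comparison always includes baseline ODQ as a covariate, fixed in advance and outside any stepwise step, either as ANCOVA or as a mixed model with baseline as a covariate. The effect may still be reported as change from baseline. Apply the same rule to each continuous secondary outcome measured at baseline, using its own baseline value. Any stepwise modelling can stay as a separate exploratory analysis. If a fuller analysis plan already says this, it need only be confirmed. The cost is a sentence or two of wording: the baseline values are already collected, and neither sample size nor visits change.
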